#### Sample size calculation

To calculate the sample size for this study we used data from the Functional Mobility Test (FMT). The FMT was designed to evaluate an astronaut’s ability to complete challenging locomotor maneuvers similar to those encountered during an egress from a space vehicle following long-duration space flight [20]. To perform the FMT subjects walked at a self-selected pace through an obstacle course set up on a base of medium density foam. The foam provided an unstable surface that increased the challenge of the test. The 6.0 m × 4.0 m course consisted of several pylons and obstacles made of foam. Subjects were instructed to walk through the course as fast as possible without touching any of the objects on the course. FMT data were used to calculate the sample size as it is the only pre/post flight data currently available with the longest recovery times (~15 days). If the other tests that are used in this study are similar to the FMT in sensitivity to spaceflight, we would fully expect to reject H_0_ for all tests. For example, from FMT results on 18 long-duration international space station (ISS) subjects, we found the mean change in log transit times to be 1.68 log sec with a standard deviation of 0.60 log sec [20]. With such a large signal-to-noise ratio and normally distributed differences the power of the t-test against H_0_ is virtually 1.0, even with as few as 10 subjects. Even if an outcome has only half the sensitivity of the FMT to spaceflight, the power with 10 subjects would still be 0.975. However, it is also important to have enough subjects to accurately estimate the mean change. If the sensitivity of a test to spaceflight were similar to that of the FMT, it would take about 13 subjects to produce a coefficient of variation of 10% for the estimated mean change post flight with respect to preflight performance. Therefore, under the assumption that sensitivities are comparable, we will require 13 long-duration astronaut subjects. We plan to target 15 subjects so we have a reserve of 2 subjects to account for subject attrition.

By including at least as much bed rest participants and control group participants as astronauts, we will ensure enough power to detect potential changes over time for these populations too.

#### Informed consent

Written informed consent will be obtained from all participants. The current studies were approved by the institutional review boards of the University of Michigan, the University of Texas - Medical Branch (UTMB), and NASA. All studies are being conducted in accordance with the declaration of Helsinki.

#### Remuneration

The astronauts will not receive remuneration for their participation. Bed rest subjects will receive $10 per hour for their participation in addition to a lump sum they receive for participating in the bed rest study. Control subjects will receive $10 per hour for their participation.

## Methods

### Behavioral assessment

Table 2 gives an overview of the cognitive behavioral measures. In general all flight and normative subjects will perform the following behavioral tests while seated in a chair with additional constraints as noted in each tests. For the bed rest and normative subjects the following behavioral tests are performed while lying down in bed supine or on their sides with their superior-inferior axis parallel to the ground.

**Table 2 T2:** Cognitive behavioral measures

**Neuropsychological test**	**Functional area assessed**	**Outcome measure**	**Range**	**Trial (s)**	**Maximum time per trial (seconds)**
Thurston’s card rotation task [61]	Spatial working memory	Number correct^a^	1-20	1	180
Cube mental rotation task [62]	Spatial working memory	a) Number correct^a^	1-26	26	10
		b) Response time (seconds)^b^	0-10		
Rod and frame test [63]	Field perception & dependency	Absolute deviation from vertical (degrees)^b^	0-18	8	n/a
Digit symbol substitution task of the WAIS [64]	Processing speed	a) Number of correctly substituted letters^a^	0-140	1	n/a
		b) Time to complete (seconds)^b^	n/a		
Purdue pegboard test [65]	Dexterity and bimanual coordination	Time needed to put 25 pairs of pins in the board (seconds)^b^	n/a	1	n/a

WAIS = Wechsler adult intelligence scale; ^a^higher score indicates better performance; ^b^less indicates a better performance.

*Spatial working memory* will be assessed with **a**) Thurston’s card rotation task [61]: each item gives a drawing of a card cut into an irregular shape. To its right are six other drawings of the same card, sometimes merely rotated and sometimes turned over to its other side. The subject indicates whether or not the card has been turned over; and **b**) cube mental rotation task [62]: Similar to a), except that target and test shapes are depicted as an assemblage of three-dimensional cubes. These cubes are modeled on those initially developed by Shepherd & Metzler. A three dimensional shape is presented on a computer screen for 3 seconds, followed by a blank screen for 2 seconds. After the delay, two 3D cube images will appear on the screen, of which one will be matching and the other will not be a match of the previous shape. The new shape will be rotated in roll, pitch and yaw with respect to the previous shape. Subjects will be asked to imagine turning of the new image to determine which of the two is a rotated version of the prior object. Subjects will respond by pressing the appropriate key on a gamepad provided them (left or right arrow for the match). The task will consist of 26 trials. Accuracy and response time will be recorded for both tests a and b.

*Field perception and field dependency* will be measured with the Rod and Frame Test (RFT; see Figure 2) [63]. The RFT is used to determine whether an individual is more or less visually dependent. The RFT consists of a screen where a rod is viewed in a number of different degrees of tilt. A tunnel-like frame (0.6 m) that surrounds the rod is projected towards the subject. Both the degree of tilt of the tunnel frame and the degree of tilt of the rod can be altered. The subject sits in the dark, with the tunnel framing their face, thus removing all earth-fixed visual cues. The subject is then required to align the rod to the upright vertical position by the use of a manual controller. A subject able to successfully align the rod to upright is said to be visually independent. Conversely, if a subject aligns the rod with a tilt bias in the direction of the tilted frame they are classified as visually dependent. The test will be repeated for up to eight trials for two random starting tilt positions of the frame and or the rod (±18°). Proprioceptive cues from the plantar sole contacts with the ground will be limited to the heels by asking subjects to extend their legs during seated trials. The subjects will be scored in degrees of deviation from vertical [63].

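### The rod and frame score in Table 2 drops the direction that defines visual dependence, so added noise or offset after flight could be read as greater dependence

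*Protocol article*

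**What the plan says.** Both statements are in the protocol article under Behavioral assessment.

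- **Table 2** assigns the test to "Field perception & dependency". The outcome is "Absolute deviation from vertical (degrees", with a range of 0 to 18, eight trials, and a footnote that "less indicates a better performance".
- **The Rod and Frame Test paragraph** gives the purpose: "The RFT is used to determine whether an individual is more or less visually dependent". The low end is defined by accuracy: "A subject able to successfully align the rod to upright is said to be visually independent". The high end is defined by direction: "if a subject aligns the rod with a tilt bias in the direction of the tilted frame they are classified as visually dependent".
- **On trials**, the paragraph says "The test will be repeated for up to eight trials for two random starting tilt positions of the frame and or the rod", with tilts of plus or minus 18 degrees.
- **On scoring**, it says only "The subjects will be scored in degrees of deviation from vertical".

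The article gives no score signed relative to the frame and no separate measure of setting variability.

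**The concern.** Dependence is defined by the direction of the error, and the outcome discards direction. Settings scattered evenly around vertical, settings shifted by the same amount whichever way the frame leans, and settings pulled toward the frame can all give the same score. Only the last is visual dependence as the article defines it.

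This matters here because the Background (Motor behavior) reports disturbed spatial orientation and eye-hand coordination after flight and attributes most vestibulo-motor disturbance to reorganised otolith information. The rod is set with a manual controller in the dark. Less precise settings or a shifted perceived vertical are therefore plausible without any change in reliance on the frame. Flight subjects are tested seated and bed rest subjects lying down, so a posture-related offset, if there is one, would also enter the comparison between those groups. The Hypotheses section predicts neuroanatomically selective correlations between brain change and function. A score that mixes three components cannot show which of them a brain change follows.

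**Working it through.** The article gives no sample size, power or expected change for this test, so there is no figure of its own to reproduce. The check asks how far the score moves when the frame effect does not change.

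**Inputs from the article:** unsigned deviation, range 0 to 18; up to eight trials; tilts of plus or minus 18 degrees; 13 astronauts (Sample size calculation).

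**Assumed, because the article gives no values:** normal errors; setting SD s between 1 and 4 degrees; mean frame bias m between 0 and 4 degrees; absolute value taken on each trial.

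**Step 1: expected absolute score.** For a setting with mean m toward the frame and SD s, the folded-normal mean is

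E|X| = s·√(2/π)·exp(−m²/2s²) + m·[1 − 2Φ(−m/s)].

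- m = 0: s = 2 gives 2 × 0.798 = 1.60; s = 4 gives 4 × 0.798 = 3.19. The score doubles with no frame effect at all.
- m = 3, s = 2: 1.596 × 0.325 + 3 × 0.866 = 0.52 + 2.60 = 3.12.
- m = 3, s = 4: 3.192 × 0.755 + 3 × 0.547 = 2.41 + 1.64 = 4.05. Ratio 4.05 / 3.12 = 1.30, a rise of 30%.
- m = 4: s = 1 gives 4.00; s = 2 gives 4.03. The rise is negligible.

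**Step 2: constant offset.** With no frame effect, an offset of 2 degrees and s = 1, the same formula gives 2.02 degrees. That equals the score of a subject with a true 2-degree frame bias and s = 1.

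**Step 3: what a paired test would report.** Simulation: 13 subjects, eight trials each (four per frame side), frame bias unchanged, only the setting SD rising, 3,000 runs, paired t-test at two-sided 0.05. Bias varied between subjects, with SD 0.5, 0.5, 1 and 2 degrees at mean bias 0, 1, 2 and 4.

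| Mean bias | Setting SD, before to after | Mean rise in absolute score | Significant, absolute | Significant, signed toward frame |
|---|---|---|---|---|
| 0 | 1 to 2 | 0.75 | 99.9% | 5.2% |
| 1 | 1 to 2 | 0.61 | 94.0% | 5.0% |
| 2 | 2 to 4 | 1.22 | 93.3% | 5.6% |
| 4 | 1 to 2 | 0.13 | 9.3% | 5.0% |

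Over all 16 scenarios run, the absolute score was significant in about 5% to 100% of runs and the signed score in about 4% to 6%.

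**Step 4: how much depends on taking the absolute value per trial.** Suppose it were taken of the mean of eight balanced trials, each signed toward the frame. The relevant SD becomes s/√8, which is 0.71 at s = 2 and 1.41 at s = 4. At m = 3 the score goes from 3.00 to 3.02, a rise of 0.02 against 0.93 per trial. At m = 0 it goes from 0.56 to 1.13, which still doubles but from a much lower level. A constant offset cancels between the two sides.

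**The case against.** - **The score is a legitimate measure of something the table names.** The functional area includes field perception as well as dependency, and visual independence is defined by setting the rod upright, which a score of zero meets exactly. A less precise or shifted vertical after flight would be a real change in field perception. This stands: the score is non-specific rather than meaningless. It does not answer the problem for the dependency half, which the article defines by direction.
- **Trial-level scoring may be fixed elsewhere.** Table 2 is an overview and the paragraph cites a source for the scoring. The article does not say whether the absolute value is taken per trial or of an average, and Step 4 shows that this matters. The conclusion must therefore be conditional on per-trial scoring. Still, the article itself names the outcome as absolute with a range starting at 0, and an analysis following it would lose the sign.
- **The premise about noise is inferred.** The article reports more variable muscle activation and joint motion after flight, but nothing on rod settings. This stands.
- **The trials may not support a signed score as they are.** Eight is a maximum, positions are random, and the tilt may be of the frame, the rod or both. Balanced frame trials are not guaranteed. This stands and is reflected in the fix.

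A reader might infer that noisier settings will be scored as greater visual dependence after flight, so that any rise in this outcome is an artefact. The documents do not support that: they give no setting SD, frame bias or expected rise in either noise or offset, and where bias is several times the SD the effect nearly vanishes.

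**Conclusion.** The mismatch is in the article's own text: dependence is directional and the stated outcome is not. If absolute error is taken per trial, frame bias, constant offset and setting variability are confounded, and a rise in noise or offset could be mistaken for greater visual dependence. For noise, the direction of the error is certain, because at a fixed bias more noise can only raise the score. Its size is not knowable from the documents. It ranges from a doubling (zero bias, SD 2 to 4) through 30% (3-degree bias, same SDs) to almost nothing (4-degree bias, SD 1 to 2), all under assumed normal errors.

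The reach is limited. This is one of many behavioural and imaging outcomes, the sample size rests on the Functional Mobility Test, and no main conclusion depends on this score alone. It should be corrected because sign cannot be recovered if only absolute values are kept.

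**What to change.** 1. Record the frame tilt and the signed rod setting on every trial.
2. Ensure that each session includes frame-tilted trials on both sides, preferably in equal numbers.
3. Make the frame effect the visual-dependence outcome: half the difference between the mean settings with the frame at +18 and at −18 degrees, positive toward the frame. If a setting equals offset + bias × side + error, half the difference estimates the bias and half the sum estimates the offset.
4. Report the constant offset and the within-session SD (computed within frame side) separately.
5. Keep absolute deviation as a secondary measure of overall accuracy, and state whether it is taken per trial.

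The cost is a change to Table 2 and the scoring, balanced allocation of the existing trials, and less direct comparability with studies that report absolute error, which item 5 largely preserves. No additional testing time is needed if the trials already planned can be allocated to both frame sides.

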**Figure 2 F2:**
[figure not shown]
Rod and Frame test.

*Processing speed* is measured with the digit symbol substitution task of the Wechsler Adult Intelligence Scale-Revised (WAIS-R) [64]: For this paper and pencil test subjects have to match digits with symbols. A key of nine digit-symbol pairs is printed on top of the page. Subjects have to complete the test as fast as possible by writing down the corresponding symbol for each of 140 digits on the page. The score is the time taken to complete the task and the number of correctly matched digits.

*Bimanual coordination* is measured with the Purdue Pegboard test [65]: The test requires participants to manipulate small pegs using both hands simultaneously to put pegs into parallel rows of holes. We measure the time taken to complete all 25 pairs on the board.

*Posture control* will be assessed with: **a**) a computerized dynamic posturography system (Equitest, NeuroCom International, Clackamas, OR) [66]. This system can be used to systematically parse out changes in the visual, vestibular and proprioceptive contributions to postural equilibrium control (see Figure 3). To perform these tests subjects stand quietly on force plates during various combinations of visual and proprioceptive input and are asked to maintain upright stance for 20 s trials. In this study, trials will be performed only with eyes closed and a sway-referenced base (Sensory Organization Test 5) with head erect and while subjects perform dynamic head tilts (forward, backward, or actively moving at 0.33 Hz paced by an audible tone). This condition assesses vestibular control of posture. Assessment time is approximately 10 minutes; **b**) The Functional Mobility Test (see Figure 4) [20]: In each test session subjects will be instructed to “walk without touching any of the obstacles on the course as quickly and as safely as possible without running”. The first half of the 6.0 m × 4.0 m course is set up on a stable hard floor. The second half of the course is set up on a base of 10 cm thick, medium-density foam (Sunmate Foam, Dynamic Systems Inc. Leicester, NC, USA), which makes proprioceptive inputs unreliable during ambulation. The course consists of the following obstacles: 1) a “portal” constructed of two successive 31 cm high Styrofoam blocks placed on concrete surface, with a horizontal foam bar hung from the ceiling between these blocks, the height of which is adjusted to that of the crewmember’s shoulders requiring crewmembers to bend at the waist or lower themselves to avoid hitting the bar hung from the ceiling and balance on a single foot on the stable hard surface while stepping over the barrier; 2) four foam pylons arranged in a “slalom” fashion on the concrete floor, which requires the subject to change heading direction continuously; 3) a 46 cm high Styrofoam block placed on the foam surface which forces the crewmember to balance on one foot on a stable hard surface (floor) while clearing the obstacle and stepping onto the compliant (foam) surface; 4) a gate on the foam surface with edges defined using two foam pylons hung from the ceiling, the width of which is adjusted to the width of the crewmember’s shoulders, so they have to walk between the pylons sideways; and 5) another “portal” (see 1)), but this time placed on the foam surface as the base support.

**Figure 3 F3:**
[figure not shown]
Computerized Dynamic Posturography.

**Figure 4 F4:**
[figure not shown]
The Functional Mobility Test.

The crew member once instructed will release the buckle on the chair and continue the course in the following order: 1.) crosses one portal on the stable hard surface; 2) walks on the floor through the vertical “slalom” pylons; 3) turns to the left and presses a button on the wall; 4) turns around and steps over the 46 cm high Styrofoam block; 5) the subject now enters the medium density foam course and presses the button on the wall; 6) the subject turns around and walks through the gate; 7) crosses the second portal on the compliant foam surface; and 8) ends by crossing the first portal. Please note the numbers besides the arrows in Figure 4 denote the order of progression through the course as described above.

This task will be performed ten times. Subjects will be allowed to rest between trials, especially immediately after flight, and all ten trials will be completed within a 10-minute window. To prevent injury from falling, in addition to the medium density foam on the floor, subjects will wear a harness while being monitored by a “spotter”. The primary performance metric will be time to complete the course and number of obstacles hit. Time metrics will be obtained with an optical timing system (Event Timer Pro, Computer Products for Education, Kingston, PA, USA) placed at strategic points on the course to obtain intermediate time measures.

### Vestibular function

The sound-evoked ocular Vestibular Evoked Myogenic Potential (oVEMP) and colic VEMP (cVEMP) will be elicited by a 500 Hz (8 ms, rate 3 Hz) pure tone of up to 130 dB SPL [67,68] delivered via calibrated headphones as subjects lay supine on a gurney (see Figure 5) [69,70]. Auditory stimuli will be presented monaurally. The vibrotactile-evoked ocular VEMP (oVEMP) will be elicited by a vibrotactile pulse presented at the rate of 1 Hz on the side of the forehead as subjects lay supine on a gurney (see Figure 6) [71].

**Figure 5 F5:**
[figure not shown]
The sound-evoked ocular Vestibular Evoked Myogenic Potential (oVEMP) and colic VEMP (cVEMP).

**Figure 6 F6:**
[figure not shown]
The vibrotactile-evoked ocular Vestibular Evoked Myogenic Potential (oVEMP).

In a couple of trials, subjects will rotate and raise their heads to contract the sternocleidomastoid muscle for measuring the cVEMP responses. In a separate couple of trials for measuring the oVEMP responses since the response is dependent on gaze direction, subjects will be directed to gaze approximately 25° above straight ahead in semi-darkness.

For the oVEMP electromyograms will be recorded with active bipolar electrodes (Delsys Inc., Boston, MA) on the infraorbital ridge 1 cm below the eyelid with a reference electrode on the chin or sternum or knee cap or the ankle. For the cVEMP electromyograms will also be recorded with active bipolar electrodes from sterocleidomastoid muscles while subjects contract their neck muscles by turning their head by 90 deg and lifting them. The EMG potentials will be amplified, band-pass filtered using a Bagnoli™ Desktop EMG System (Delsys Inc., Boston, MA, USA). This EMG signal is sampled at 10 kHz and the data stimulus onset to 100 ms will be averaged over 100 trial repetition for the auditory VEMP and 24 trial repetitions for the vibrotactile VEMP. The typical oVEMP EMG response is an excitatory potential with first peak occurring at 11–12 ms and second peak at 18 ms. This requires a total recording time of approximately 38 or 29 seconds per trial which includes 5 seconds of 0 dB SPL or no vibrotactile stimulation at the beginning of the protocol. The primary dependent measures consist of the latency and peak-to-peak amplitude from the EMG signals, which will be normalized to EMG levels at the beginning of the protocol.

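### cVEMP amplitude is scaled to EMG from the start of the trial, so a pre/post difference in neck-contraction drift during the trial would be scored as a vestibular change

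*Protocol article*

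**What the plan says.** All of this stands in the protocol article, section Vestibular function, including the text after Figure 6.

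- **Stimuli.** The auditory VEMP uses a "500 Hz (8 ms, rate 3 Hz) pure tone of up to 130 dB SPL". The vibrotactile oVEMP is "elicited by a vibrotactile pulse presented at the rate of 1 Hz on the side of the forehead".
- **Contraction.** The cVEMP is recorded from the sternocleidomastoid "while subjects contract their neck muscles by turning their head by 90 deg and lifting them". The oVEMP is recorded below the eyelid during upward gaze.
- **Averaging.** For the EMG signal, "the data stimulus onset to 100 ms will be averaged over 100 trial repetition for the auditory VEMP and 24 trial repetitions for the vibrotactile" recordings.
- **Duration.** "This requires a total recording time of approximately 38 or 29 seconds per trial". Part of that time is an unstimulated opening, described by the clause "which includes 5 seconds of 0 dB SPL or no vibrotactile stimulation at the beginning of the protocol".
- **Reference for scaling.** The measures named as primary are "latency and peak-to-peak amplitude from the EMG signals, which will be normalized to EMG levels at the beginning of the protocol".

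The article names no EMG reference taken during stimulation, no target contraction level and no monitoring of contraction.

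**The concern.** Scaling amplitude to EMG makes sense only if amplitude depends on how hard the muscle is contracting, so the plan itself accepts that dependence. It then measures contraction once, before any stimulus, and applies that value to responses gathered over the following half minute. A change in contraction during the hold alters the numerator and leaves the denominator untouched.

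An equal change in every session would cancel in the pre/post comparison. A different change would not. A difference is plausible in this study: Central nervous system plasticity lists muscle unloading among the peripheral changes that compete with a brain explanation, and Multitude of risk factors lists unloading among the microgravity effects that bed rest reproduces. A vestibular index that takes in a change in muscle endurance would blur explanations that the study wants to separate. The control-group de-trending offered in the Discussion corrects drift that controls share, so it could not be relied on to remove a component specific to exposure.

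**Working it through.** **1. Where the reference lies (plan's own figures).** Recording time = stimuli / rate + 5 s.

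- Auditory: 100 / 3 Hz + 5 = 33.3 + 5 = 38.3 s. The article says about 38 s.
- Vibrotactile: 24 / 1 Hz + 5 = 29.0 s. The article says 29 s.

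Both figures reproduce only if the 5 s precede all stimulation. The article uses the same phrase for the position of those 5 s and for the EMG reference, so I read the reference as this opening period. If the start of the whole session were meant, the reference would lie even further from the responses.

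**2. How far the responses lie from the reference.** Auditory responses occupy 33.3 / 38.3 = 87% of the trial, all of it after the reference period.

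**3. Effect of drift.** These are assumptions, not figures from the article: the neck is already contracted in the opening 5 s; amplitude at each stimulus is g × EMG at that moment, with vestibular gain g the same in both sessions; EMG falls linearly by a fraction d from the first stimulus to the end (negative d means a rise).

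- Mean EMG during stimulation = E0 × (1 - d/2).
- Reference EMG = E0.
- Scored amplitude = g × (1 - d/2).
- Apparent change = (1 - d_post/2) / (1 - d_pre/2) - 1.

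| Drift before | Drift after | Calculation | Apparent change |
|---|---|---|---|
| 10% fall | 10% fall | 0.95/0.95 - 1 | 0% |
| 10% fall | 20% fall | 0.90/0.95 - 1 | -5.3% |
| 10% fall | 30% fall | 0.85/0.95 - 1 | -10.5% |
| 20% fall | 40% fall | 0.80/0.90 - 1 | -11.1% |
| 30% fall | 10% fall | 0.95/0.85 - 1 | +11.8% |
| none | 20% rise | 1.10/1.00 - 1 | +10.0% |

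Summing over the 100 individual stimuli gives nearly the same values. For 10% to 20%, 10% to 30% and 20% to 40%, the results are -5.2%, -10.4% and -11.0% if the decline starts at 5 s, and -5.3%, -10.7% and -11.5% if it starts at 0 s.

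**4. Same model with concurrent EMG.** Each response divided by EMG at the same moment is g × E / E = g, so the apparent change is 0% for any drift.

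**5. Room for a concurrent reference.** At 3 Hz the interval is 1000/3 = 333 ms. Less the 100 ms epoch, about 233 ms remain before the next stimulus. The article states sampling at 10 kHz.

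**The case against.** The strongest reply is that the larger problem is already handled. Scaling to the level at the start of each trial removes differences between sessions in how hard the subject contracts. What is left is only a difference between sessions in drift over about 33 s, and the article has no data showing that one exists. Holding the head up is a roughly constant load, so a large fall in EMG is not self-evident. The unloading passages do not mention the neck. VEMP amplitude appears in neither Objectives nor Hypotheses, and the VEMP paradigm under Functional MRI paradigms runs without EMG recording. All of this stands. It limits the size and weight of the point, but it does not make the opening 5 s a good reference for responses recorded later.

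A reader might go further in four ways that the article does not support.

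- **That fatigue would push the result towards the study hypothesis.** Hypotheses predicts change in brain measures and gives no direction for VEMP. Drift could go either way.
- **That all VEMP amplitudes are affected.** The mechanism needs a held neck contraction, so it concerns the cVEMP only.
- **That latency will be divided by EMG.** The relative clause can attach to amplitude alone. This is loose wording, not a stated plan.
- **That EMG between epochs is discarded.** The 100 ms window is what is averaged. The text does not say that the rest of the recording is dropped.

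**Conclusion.** The point holds for the cVEMP. The stated reference corrects for starting contraction but not for drift during the trial, and any pre/post difference in that drift enters the vestibular measure. Whether such a difference will occur, in which direction and how large, cannot be told from the article. Under the linear, proportional model the distortion is roughly half the difference in drift, or slightly more when the muscle already declines at baseline: from nothing to about 11% in either direction over the values tried. These are illustrations, not estimates. A claim that fatigue will produce a falsely reduced vestibular response goes beyond the evidence. Severity is minor to moderate: the measure is primary within the VEMP test, no stated objective rests on it alone, and a better reference should be available from the same signal.

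**What to change.** In Vestibular function:

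1. For the cVEMP, normalize peak-to-peak amplitude to mean rectified EMG from the same stimulation period, for example from a pre-stimulus window for each sweep, applied before averaging.
2. Keep normalization to the opening 5 s as a sensitivity analysis. A disagreement between the two would show that drift matters.
3. Report cVEMP EMG level by session, so that a reader can see whether contraction changed.
4. Reword the sentence so that normalization applies to amplitude only and latency is given in ms.

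The oVEMP rule need not change on this account.

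**Cost.** The EMG between epochs must be retained, and processing takes a little more work. No recording time, visit or procedure is added.
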